#### Bleeding upon marginal probing (BOMP)

Gingival bleeding will be assessed with the Bleeding on Marginal Probing index (BOMP). This will be used to score the condition of the gingiva according to the method described by Van der Weijden et al. (1991). In summary, a periodontal probe (tapered tine, tip diameter 0.5 mm; Hu-Friedy, Liemen, Germany) runs along the soft tissue wall at the orifice of the pocket – i.e., the marginal gingiva – at an angle of approximately 60° to the longitudinal axis of the tooth [37]. To determine whether probing elicited marginal bleeding (score 1) or not (score 0), we will assess the mesio-vestibular, vestibular, disto-vestibular sections of the vestibular surfaces of the first premolar, canines and incisors. The presence or absence of bleeding will be scored within 30 s of probing. To obtain a total number of bleeding sites per participant, all scores for the analysis will be summed.

To ensure the reliability of the clinical measurements, the clinical examiners at each site (a dentist and student dental hygienists) will be trained and calibrated by an experienced ACTA University examiner two weeks before the start of the study. The calibration will involve a separate group of ten people.

It will not be possible to determine inter-rater reliability by performing the clinical measurements twice, as the first set of measurements will affect the results of the second: plaque will removed by the probe used to determine the plaque score, and more marginal bleeding might be elicited by the second probing of marginal gingiva. For this reason, one examiner will perform the clinical measurements and another examiner will observe them, and then give a second independent judgement. The inter-rater reliability will thus be determined by comparing the scores made by both examiners. This will be done in a random sample of 10% of the measurements. To determine the inter-rater reliability of the primary outcome measures the Intra-class Correlation Coefficients (ICC) will be calculated.

#### Process evaluation

A process evaluation will be performed to examine intervention fidelity (i.e., the extent to which participants comply with the intervention); and participants’ experiences with the intervention program, including the perceived effectiveness of various components of the WhiteTeeth app.

Information on intervention fidelity will be collected through the app. For medical-ethical reasons, the app users’ data will not be uploaded automatically. Instead, participants will have to send it themselves from their smartphone to the database. During intervention allocation, participants will be informed about the collection of their users’ data, and will be asked to send it via the app each week. At 6 and 12 weeks follow-up, all participants will be reminded to send their user’s data via the app. User’s data consists of (1) the week that the users’ data is sent, (2) the login code of the app, (3) the total number of selfies, (4) the total number of clicks on the selfie, (5) the total number of times that the brushing timer is opened, (6) the average number of minutes brushed registered by the brushing-timer, (7) the action plans that are entered into the application, (8) the goals that were set, (9) the number of times that they watch a video about (I) dental plaque and cleaning their teeth either with (II) a manual toothbrush, an (III) electric toothbrush, or (IV) interdental brushes; and (10) their initial motives for cleaning their teeth.

At 12 weeks follow-up, the participants’ experiences with the intervention program will be examined in a short questionnaire consisting of open and closed questions (See Additional file 4 for questionnaire part III).

To maximize retention of participants, all participants will receive a letter at baseline on the importance of adhering to the intervention and on participation in the follow-up measurements. To promote their active participation in the study, participants will receive monetary compensation (€10) at the end of the trial.

### Data-management

All data will be recorded using FileMaker Pro© 15 database. Separate FileMaker Pro forms have been designed for both the clinical measurements and the questionnaires.

The researchers will register clinical data on tablets. To fill in all questionnaires, participants will use the tablets in a separate room. To ensure that appropriate help and guidance can be given when needed, this will be done in the presence of one of the researchers. To minimize data-entry errors, the forms have inbuilt check-and-skip rules. FileMaker Pro will allow us to export the data safely from tablets to SPSS Statistics database. For participants who withdraw from the trial, any data collected up to the withdrawal date will be retained and included in the analyses.

Names, mobile phone numbers and addresses will not be recorded in the same forms as sensitive data. Each participant will be given a unique identification number. Each participant will send their weekly user’s data to a secure server owned by ACTA University. Only the principal and the co-principal researchers will have access to the participants’ personal data. All data will be saved on password-protected computers and tablets. When the study has been completed, all personal identifiers will be deleted. Data will be kept in stored digitally at the coordinating center (ACTA) for 5 years after completion of the study.

### Blinding

The participants in this study cannot be blinded for the intervention allocation after randomization. To ensure the blindness of assessors and clinicians, the principal researcher will ask the participants not to communicate with outcome assessors or their clinicians on whether they use the app.

### Sample size

The sample-size calculation will be based on the primary outcome measure, the modified Silness and Loë plaque index. Between treatment groups we have assumed a 0.35 difference in mean change at week 12 [38]. The required sample size is 2 × 63 patients (setting α = 5% (two-tailed), a standard deviation (s) of 0.7, and the power (1-β) = 0.80) [39]. Allowing for an expected loss of 15%, a sample of 73 patients is needed in each group.

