**Methods/design:**

The RCT has two conditions: an experimental group that will receive the WhiteTeeth app in addition to care as usual, and a control group that will only receive care as usual. Care as usual will include routine oral-health education and instruction at orthodontic check-ups. In the western part of the Netherlands 146 participants will be recruited from four orthodontic clinics. Data will be collected during three orthodontic check-ups: baseline (T0), 6 weeks of follow-up (T1) and 12 weeks of follow-up (T2). The primary study outcomes are the presence of dental plaque (measured with a modified Silness and Loë Plaque Index); and gingival bleeding (measured with the Bleeding on Marginal Probing Index). Secondary outcomes include changes in self-reported oral-health behaviors and its psychosocial factors identified by the HAPA theory, such as outcome expectancies, intention, action self-efficacy, coping planning and action control.

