### Participants and recruitment

One hundred forty-six orthodontic patients aged 12 to 16 will be recruited in four orthodontic clinics in the western Netherlands. The study sites will be eligible if (1) standard oral-health instructions are administered according to the clinical guidelines of the department of orthodontics at the Academic Centre for Dentistry Amsterdam (ACTA) (See paragraph ‘Care as usual’); if (2) the clinicians are orthodontists registered in the Dutch orthodontic specialist register, or are postgraduate orthodontic students supervised by a registered orthodontist; if (3) the orthodontists are willing not to change their method of providing oral-health education or instructions during the study period (care as usual); if (4) there is scope for the researcher to inform patients about treatment allocation and the app (in the case of participation in the intervention group); and if a dental chair is available for the oral-health assessments. We will include the same number of participants from each study site.

Before the study starts, a presentation on it will be given at the eligible clinics. Patients who meet the eligibility criteria (Table 1) will be informed about the study by their clinician. They will then receive an information letter and an informed consent form (see Additional file 1), and have two visits before the baseline measurements. The letter will include information on the intervention, the study design, and ethics. Patients will be recruited over a 3-month period. The baseline assessment will be scheduled after patients’ and their parents’ written informed consent has been received.

**Table 1 Tab1:** Eligibility criteria

Patients will be eligible for the study if they meet the following criteria:
- Boys or girls aged 12 to 16.
- For at least 6 weeks, they must have maxillary and mandibular fixed orthodontic appliance therapy, which consists of bonding at least premolar-to-premolar with edgewise appliances and their modifications.
- They have not been scheduled for removal of fixed orthodontic treatment before the end of the study.
- They have no physical and/or mental disabilities that will impede their ability to perform their own oral hygiene activities.
- They are not engaged in other oral-health education or research program.
- They do not have enamel and dentine dysplasia and/or craniofacial malformation (e.g. cleft).
- They have a sufficient command of the Dutch language.

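### 73 per group falls just short of the required 63 after the expected 15% loss; the effect is about one evaluable patient per group

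*Protocol article*

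**What the plan says.** The Sample size section of the protocol article bases the calculation on the modified Silness and Loë plaque index. Its inputs are:

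- effect: "Between treatment groups we have assumed a 0.35 difference in mean change at week 12"
- spread: "a standard deviation (s) of 0.7"
- significance level: "setting α = 5% (two-tailed"), that is, two-sided 5%
- power: "the power (1-β) = 0.80"

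From these it concludes: "The required sample size is 2 × 63 patients". It then enlarges the number for dropout: "Allowing for an expected loss of 15%, a sample of 73 patients is needed in each group". The formula for this last step is not given. The abstract carries the resulting total: "146 participants will be recruited from four orthodontic clinics".

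**The concern.** The section gives three linked numbers: 63 required per group, 15% expected loss, and 73 enrolled per group. If the allowance does its job, 73 less 15% should leave at least 63. It leaves slightly fewer.

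This pattern arises when the loss percentage is applied to the number required instead of the number enrolled. The loss falls on those enrolled, so the enrolled number must be the required number divided by the retained fraction.

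What is at stake is the accuracy of the sample-size statement. As written, 73 per group, 15% loss and 80% power do not hold together, and the statement may well be carried into the results paper.

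**Working it through.** **Inputs** (all from the Sample size section): difference 0.35, SD 0.7, two-sided α = 0.05, power 0.80, 1:1 allocation, required n = 63 per group, expected loss 15%, enrolled n = 73 per group.

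**Step 1. Reproduce the 63.** Normal approximation for two means:

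n = 2 × (z₀.₉₇₅ + z₀.₈₀)² × (SD / difference)² = 2 × (1.960 + 0.842)² × (0.7 / 0.35)² = 62.79, rounded up to **63**.

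This matches the article exactly, so the normal approximation is used as its method from here on.

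**Step 2. Look for the source of the 73.**

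- Loss added to the requirement: 63 × 1.15 = 72.45, rounded up to 73. This matches.
- Requirement divided by the retained fraction: 63 / 0.85 = 74.12, rounded up to 75. This does not match.
- Unrounded requirement divided: 62.79 / 0.85 = 73.87. This gives 73 only if rounded down.

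The first route is the natural reading, but it is an inference. The next step does not depend on it.

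**Step 3. Apply the stated loss to the stated enrolment.**

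- Per group: 73 × 0.85 = 62.05, against 63.
- In total: 146 × 0.85 = 124.1, against 126.
- One more per group is still marginally short: 74 × 0.85 = 62.9. With 75: 75 × 0.85 = 63.75, which suffices.

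**Step 4. Loss that 73 per group can absorb.** 1 − 63/73 = 10/73 = 13.7%. That is 10 patients per group, where 15% of 73 is 10.95.

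**Step 5. Power by the same normal approximation.** Power = Φ(√(n/2) × 0.35/0.7 − 1.960).

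| Evaluable per group | √(n/2) × 0.5 | Power |
|---|---|---|
| 63 | 2.806 | 80.1% |
| 62 | 2.784 | 79.5% |

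The shortfall costs about 0.6 percentage points. Put another way, 62 per group has 80% power for a difference of 2.802 × 0.7 × √(2/62) = 0.352 instead of 0.35.

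**The case against.** The strongest reply is that this is too small to matter.

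- **Size.** The shortfall is about one patient per group, well inside the uncertainty of the inputs. The SD is given to one decimal. Values from 0.65 to 0.75 would move the requirement from 62.79 × (0.65/0.7)² = 54.1, so 55, to 62.79 × (0.75/0.7)² = 72.1, so 73 per group. That range dwarfs a correction of two patients. This stands, and it is why the point is minor.
- **Planned analysis.** The Data-management section keeps data collected up to withdrawal, and the Statistical analysis section plans intention-to-treat linear mixed models with baseline covariates. A participant lost after the 6-week visit can still contribute, so counting losses as contributing nothing is pessimistic. This also stands, although the gain cannot be quantified because no within-patient correlation is given. It does not repair the sentence itself, which rests on a week-12 difference with its own loss allowance and takes no credit for repeated visits.
- **Cause.** No inflation formula is shown. A reader might state as fact that the 15% was added. The exact match makes that likely, but the documents do not establish it.

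Two stronger readings also go too far. A reader might say that 63 is itself wrong because a t-based calculation gives 64, and quote 78.9% power at 62. But the normal approximation is a legitimate choice that reproduces the article's figure. The t-based power at 63 is already 79.5%, so the 78.9% mixes a change of method with the loss allowance, which accounts for about 0.6 points under either method.

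A reader might also object that 146 / 4 = 36.5 conflicts with "We will include the same number of participants from each study site" in Participants and recruitment. Recruiting 36 or 37 per clinic is ordinary rounding and changes no estimate, test or power figure. It adds no weight here.

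**Conclusion.** The point holds as a minor arithmetic inconsistency in the Sample size section. On the article's own figures, 73 per group with 15% loss leaves 62.05, not 63, and 75 would be needed to keep 63. The consequence is 79.5% power instead of 80.1%, assuming the stated difference and SD, the normal approximation, and no information from participants who are lost. If partial data contribute to the mixed model, the effect is smaller.

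A reader might infer that the trial is underpowered or should be enlarged. The documents do not support that: a difference of about half a percentage point from the nominal 80% has no practical bearing on what the trial can detect.

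**What to change.** Keep the total at 146 and correct the sentence in one of two ways:

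- state that 73 per group preserves the required 63 for losses of up to 13.7%; or
- state that at 15% loss about 62 per group are expected to remain, giving about 79.5% power under the stated assumptions.

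The corrected statement should be the one used in the results paper. As an editorial note only, the equal-numbers statement in Participants and recruitment could read 36 or 37 patients per clinic.

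The cost is one reworded sentence and a marginally lower stated power or tolerated loss. No extra patients are needed, and neither design nor conduct changes.

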### Statistical analysis

All statistical analysis will be based on the intention-to-treat (ITT) principle. The participants’ characteristics will be summarized using descriptive statistics (mean, standard deviation, frequency). Baseline data will be used to investigate the characteristics of any participants who discontinue or deviate from the trial and/or intervention. The magnitude of change over time across study groups will be examined by linear mixed models for continuous primary and secondary outcome variables, controlling for baseline variables and other covariates that may relate to the outcome.

To take account of the correlated observations within the participant, mixed-model analyses will be used. Two analyses will be performed: 1) to evaluate the overall intervention effect, 2) to evaluate the intervention effect at different follow-up times. This will be done by adding time and the interaction between time and intervention group variable into the linear mixed models. For mediation analysis, we will perform linear regressions based on Baron and Kenny’s recommendations [40]. A Sobel test will be used to test the mediating effect. A z-value greater than 1.96 and a *p*-value lower than 0.05 will indicate a significant mediating effect [41].

### Benefits and harms

Participants in the experimental condition might benefit from the intervention by achieving better oral health. Since no harmful consequences are expected from exposure to the intervention, a data-monitoring committee is not needed. Unanticipated problems or adverse events that are likely to be related to the trial will be recorded and reported to the METC at VU Medical Centre Amsterdam. Authorship of the publications emerging from the study will be decided on the basis of the guidelines of the International Committee of Medical Journal Editors.

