### Randomization

Randomization to the intervention group or control group will be performed at the patient level. A co-author who is not involved in data collection or analysis will use a random sequence generator (http://www.random.org) to allocate patients in a random sequence to the intervention or control group. In a separate room after completion of the baseline measurements, an independent researcher will tell individual participants to which group they have been allocated. If this is the intervention group, the researcher will help them install and unlock the app on their smartphone, and will also provide information on how to use it. To identify dental plaque during the intervention period, participants in the intervention group will receive twelve disclosing tablets (Gum® Red-Cote®). To prevent treatment contamination, adolescents in the control group will not have access to the intervention, as the app will be locked with a personal code that will only be provided to the adolescents in the experimental group.

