### Data collection

Figure 1 presents an overview of the data-collection procedures. Before the orthodontic check-ups at T0, T1 and T2, all participants will fill in a digital questionnaire on the tablet (Ipad® Air 2.0) in a separate room at the clinic. Next, before the orthodontic check-up, the clinical measurements will be made.

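### Adverse events are recorded only after being judged trial-related; no judge is named, and the staff who examine patients are meant not to know who uses the app

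*Protocol article*

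**What the plan says.** The rule is in the protocol article, Benefits and harms: "Unanticipated problems or adverse events that are likely to be related to the trial will be recorded and reported to the METC". The same section explains the absence of a data-monitoring committee by saying that "no harmful consequences are expected from exposure to the intervention".

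The Blinding section seeks to keep assessors and clinicians unaware of allocation: "the principal researcher will ask the participants not to communicate with outcome assessors or their clinicians on whether they use the app". Its wording concerns app use; it says nothing about symptoms.

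Other staff and instruments lie outside that restriction:

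- Randomization: after the baseline measurements "an independent researcher will tell individual participants to which group they have been allocated", and this researcher helps app-arm patients install the app.
- Data collection: before the check-ups at baseline, 6 weeks and 12 weeks, "all participants will fill in a digital questionnaire on the tablet (Ipad® Air 2.0) in a separate room at the clinic".
- Data-management: on questionnaire completion, "this will be done in the presence of one of the researchers". Whether that researcher is blinded is not stated.
- Process evaluation: at 12 weeks, participants' experiences with the program "will be examined in a short questionnaire consisting of open and closed questions".

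**The concern.** A relatedness threshold is reasonable for deciding what to send to an ethics committee. It is a poor threshold for deciding what to write down. An event left out at the start cannot be re-judged later, counted, or compared with the other arm.

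The difficulty is sharper here because the judgement needs a fact that the examining staff are meant not to have. Only the app arm receives disclosing tablets, weekly prompts to use them, daily notifications and a brushing timer. An orthodontist who sees sore gums and does not know about the app lacks the information that would connect the two.

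At stake is the harms statement of a trial in patients aged 12 to 16. According to the Discussion, its results are to guide adjustments before wider roll-out. A report of few or no adverse events could reflect the recording rule as much as the app.

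**Working it through.** The article states no adverse-event rate or threshold, so there is no planned figure to reproduce. The check is a reading of the sections together, followed by an illustration of why the size of the loss cannot be derived.

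**Step 1. What the criterion governs.** In Benefits and harms a single qualifier precedes two verbs, recording and reporting. It might attach to adverse events only, leaving unanticipated problems unfiltered. On either reading it applies to adverse events, and to recording them.

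**Step 2. Who applies it.** No section says. There are two possibilities.

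- *Clinicians or assessors judge.* Under Blinding they should not know who uses the app. They can recognise a problem caused by probing, which is done in both arms. They have little basis for linking a problem to the tablets or to an app-prompted routine. App-specific events then tend to drop out, which pulls the arms towards looking alike.
- *Staff who know the allocation judge.* The same complaint can be attributed to the app in one arm and has no app to be attributed to in the other. The chance of being recorded then depends on the arm, which can create a difference that is not real.

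The two possibilities distort in different directions, and the text does not say which applies. Neither gives an unbiased comparison.

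**Step 3. Whether another route fills the gap.** As described, none collects harms in both arms. The independent researcher appears only at allocation and installation. The researcher present at the questionnaires is there to help with completion. The 12-week experience questionnaire concerns the intervention program and its perceived effectiveness. The ten listed items of app user data include no symptom or problem.

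**Step 4. Illustration of size.** Inputs:

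- N = 73 in the app arm (Sample size: "Allowing for an expected loss of 15%, a sample of 73 patients is needed in each group").
- p = true risk of an event per patient. Not in the document; assumed 1% or 5%.
- s = share of true events that pass the filter. Not in the document; assumed 1, 0.5 or 0.1.

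Expected recorded events = N × p × s. Probability that none is recorded = (1 − p × s)^N.

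| p | s | Expected recorded | P(none recorded) |
|---|---|---|---|
| 5% | 1 | 73 × 0.05 = 3.65 | 0.95^73 = 0.024 |
| 5% | 0.5 | 73 × 0.025 = 1.83 | 0.975^73 = 0.158 |
| 5% | 0.1 | 73 × 0.005 = 0.37 | 0.995^73 = 0.694 |
| 1% | 1 | 73 × 0.01 = 0.73 | 0.99^73 = 0.480 |

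The first three rows show that filtering can turn a record that would very probably contain events into one that is probably empty. The last row shows that a low true risk leaves the record empty about half the time even with full recording. An empty record therefore cannot be interpreted without knowing s, and the document gives neither s nor p.

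**The case against.** The strongest reply is that the rule is less harmful than it looks. Its parts fare as follows.

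- **A reader might infer that blinded staff apply the filter and that the harms record will be nearly empty by design.** The document does not support this. It assigns the judgement to nobody. Participants are asked not to reveal app use, not to conceal symptoms. Unblinded contact exists at allocation, and an open-ended questionnaire exists at 12 weeks.
- **A reader might infer that control-arm events can hardly qualify.** This also goes too far. The criterion is relatedness to the trial, which includes the probing done in both arms at all three visits.
- **A reader might infer that no comparison of any harm is possible.** Gingival bleeding is a primary outcome scored in both arms regardless of cause, so a worsening in the app arm could show there. It is not a general harms measure.
- **A reader might want a bound.** With full recording and no events among 73 patients, the one-sided 95% upper limit is 1 − 0.05^(1/73) = 4.0%. Dividing by a capture share of 0.5 or 0.1 gives about 8% or 40%. These results are driven by the assumed share and are not findings about this trial.
- **The added exposure is modest.** Usual care already recommends, in both arms, brushing at least twice daily, dental aids and fluoride rinse. App users set their own goals. This stands, and it lowers the importance of the point.
- **Operational detail may sit in the full protocol.** That is fair for forms and responsibilities, whose absence from an article is not a fault. It does not answer a recording criterion that the article states outright. A fuller document that recorded everything would contradict the sentence, which would still need correcting.

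**Conclusion.** The point holds, at minor severity. For adverse events the article makes a causality judgement the condition for recording, names no one to make it, and aims to keep the examining staff unaware of the fact they would need. App-related events can be lost or captured differently by arm. The resulting record cannot support an unbiased comparison of harms, nor test the expectation of no harm on which the decision against a data-monitoring committee rests.

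The number of events lost cannot be computed from the document. The conclusion assumes that the sentence is applied as written and that no other route described in the article is meant as adverse-event collection. The primary efficacy analysis is not affected.

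**What to change.** Change Benefits and harms so that oral or other health problems since the last visit are recorded in both arms, irrespective of presumed cause. Collect them through one identical item in the existing tablet questionnaire at 6 and 12 weeks. Have relatedness judged afterwards by a named role other than the blinded assessor or treating clinician, and tabulate events by arm. The criterion for reporting to the ethics committee can stay as it is.

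Add one sentence to Blinding: the request not to discuss app use does not cover reporting a health problem.

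The cost is one questionnaire item at two visits already planned, a short table, and a one-sentence change to the participant instruction. Some unrelated events will be recorded, and a participant who reports a problem may occasionally unblind a clinician.
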